## Lifestyle Considerations

Participants must agree to not drive during the study and the study visits. This is an absolute risk avoidance approach for the safety of participants and the public in the face of very little evidence supporting the safety of cannabidiol use while operating a motor vehicle. Participants will be asked to use contraception and will include monthly pregnancy tests. Female participants on hormonal contraceptives should be advised to use an additional alternative, non-hormonal/reliable barrier method of birth control during the study. Male, female and nonbinary participants will all be encouraged to continue contraceptive precautions for up to three months after discontinuation of cannabis-based therapies. Recreational cannabis use during the study will be discouraged.

## Screen Failures

Screen failures are defined as participants who consent to participate in the clinical trial but are not subsequently assigned to the study intervention or entered into the study. A minimal set of screen failure information is required to ensure the transparent reporting of screen failure participants. Minimum information includes demographic details, screen failure details, eligibility criteria, and any serious adverse events (SAEs).

## Strategies for Recruitment and Retention

We plan to recruit 20 participants satisfying our inclusion criteria across the three chronic pain programs; Halifax, Vancouver, and Toronto. All three programs at each site manage around > 10 adolescent patients with chronic headaches in a month. Our study's sample size and dose escalation are coherent with the standard of phase 2 clinical trials. Potential participants presenting to the pain clinics across all three centres will be approached to participate in the study.

If the adolescent or parent is interested in participating in the study, a research coordinator will contact them. To improve retention, we co-developed our consent form with youth advisors. To compensate participants for their time and encourage daily data entry participants will be compensated up to $105 for the study participation, which is $15 per completed study visit, and 0.50 per daily diary entry. Adolescents and the C4T youth advisors were asked how to improve recruitment and retention into CAN-CHA. They recommended consistent follow-up and personal check-ins from the study team if a daily entry was missed for more than 2 days in a row which will be implemented in this trial.

# STUDY INTERVENTION

## Study Intervention(s) Administration

### Study Intervention Description

This study's investigational product is oil-based CBD enriched CHE, MediPharm Labs MPL-001 (CBD:THC 25:1) oil. MPL-001 is available in 30ml bottles where each ml of oil contains 2 mg of THC and 50 mg of CBD dissolved in coconut/palm-based medium chain triglyceride (MCT) carrier oil. The high-quality formulated oil has a unique flavour profile from the naturally occurring cannabis terpenes. The MPL-001 (CBD:THC 25:1) oil used in this study contains lemon-peppermint flavouring agents. Manufacturing of MPL-001 (CBD:THC 25:1) oil occurs following Good Manufacturing Practices.

### Dosing and Administration

Eligible study participants will complete a baseline phase (first month) where no investigational product will be administered for one month. At the four subsequent study visits, study participants will receive escalating doses of CBD-enriched CHE from 0.2-0.4 mg/kg/day to 0.8-1 mg/kg/day for four months, with dose increases happening monthly over four months in 0.2mg increments. Participants will self-administer the investigational product orally following a dosing calendar and all dosing calculations will be based on weight at baseline. The product comes as CHE oil, 25% of the daily dose will be administered in the morning, and the remaining 75% of the dose in the afternoon to mimic endogenous cannabinoid diurnal variation. Upon completing the baseline phase, the eligible study participants will receive a supply of study products delivered to their home from the study central pharmacy at Children’s Hospital Research Institute of Manitoba (CHRIM). Each package will include a participant-specific dosing calendar for dose confirmation, and a return envelope to the central study pharmacy at CHRIM for used bottles to be mailed back for destruction and accountability.

During visit 2, study participants will be instructed how to administer the investigational product (IP) at a dose of 0.2-0.4 mg/kg/day divided into two doses (BID, 25% dose in morning and 75% in the afternoon) for one month. Participant’s day 1 of IP dose starts the day after visit 2.

After one month of the intervention, the participants will receive new supply/supplies of the investigational product from CHRIM during visits 3 through 5 (See table 4). The 6^th^ month will include a weekly weaning period where the dose is reduced each week at the same rate as the dose escalation (0.2mg/kg/day) (See table 5). To maintain the accuracy and consistency in the dosing regimen of the study participants across all the study centres, the mid-point of the dose range will be selected to calculate the desired dose based upon the weight of the participants. Participants will be weighed on site at each study visit. However, the dose calculation will be based on the weight taken at baseline. The final dose will be calculated by rounding off the nearest 1 mg of CBD. As an exemplary 24 kg, (0.3mg/kg/day) adolescent will receive a dose of 7 mg/day. This will help achieve improved efficacy, precision in dosing and ease the administration of the MPL-001 (CBD:THC 25:1) oil to the study participants.

**Table: 4** The single escalating dose of the MediPharm Labs MPL-001 Oil from visit 2 to visit 5

| **Visit** | **Dose** | **Frequency** | **Duration** |
| --- | --- | --- | --- |
| Visit 2 | 0.2-0.4 mg/kg/day | BID | 1 month |
| Visit 3 | 0.4-0.6 mg/kg/day | BID | 1 month |
| Visit 4 | 0.6-0.8 mg/kg/day | BID | 1 month |
| Visit 5 | 0.8-1 mg/kg/day | BID | 1 month |

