*a. If participant withdraw from the study intervention prior to visit 7 but consents to stay in the study, they will be followed up till visit 7 for all the other assessments, including bloodwork, eDiary and questionnaires. Site study team will provide guidance on IP administration and follow up with participant regarding their experience of IP administration at home. IP administration will not be completed at study site during the scheduled study visit.*

*b. Document titled “C4T Baseline Safety Screening Tool for Cannabis-related interventional trials”, also called “SCR Checklist” will be used by study team to document thorough medical history at visit 1, with Common Terminology Criteria for Adverse Events (CTCAE) grade level to be applied with each reported medical history condition.*

*c. Participants will self-administer the investigational product orally following a dosing calendar and all dosing calculations will be based on weight at baseline (visit 1), unless there is a significant body weight change that would affect dosing. If participant’s body weight increases or decreases for 10% or above comparing with baseline data, site investigator will contact study PI [name] for further instructions regarding dose change or participant withdrawing. The decision will be made on a case-by-case basis to protect participant’s safety, and in the meanwhile minimize negative impact on data integrity.*

*d. Any ongoing co-existing medical condition at visit 1 will be followed up by site study team at follow-up visits to document changes.*

*e. Both urine and blood pregnancy tests will be completed at visit 1. Blood pregnancy test will be completed from visit 2- visit 7.*

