**Treatment Phase (visit 2 to visit 5)**

Before visit 2 (start of the second month) the study participants will receive CBD-enriched CHE (MPL-001) and a dosing calendar shipped to their homes before visit 2. Participants will be instructed to administer it at a dose of 0.2-0.4 mg/kg of CBD per day divided into two doses (25% in the morning and 75% in the afternoon after school). Participant-specific dose will be prescribed by site investigator. Participants will be asked to administer CHE with food.

Participants will complete monthly study visits and receive a one monthly supply of MPL-001. They will be instructed on how many drops to administer daily for the following one-month period. Participants will be asked to administer the intervention for the next month at escalating doses of 0.4-0.6 mg/kg/day then 0.6-0.8 mg/kg/day at the visit 4, and finally 0.8-1.0 mg/kg/day at visit 5. Blood samples will be drawn each month to measure the plasma concentration of CBD, THC, and its metabolites before increasing the dose, pregnancy test and liver and renal safety lab test. For all the follow-up visits, participants will be asked to provide information about PedsQL ™ Family Impact Module assessment and perception of improvement, self-directed goal attainment scaling.

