## Exclusion Criteria

An individual who meets any of the following criteria will be excluded:

1. As per the investigator judgement, the participant is not an ideal candidate due to a personal issue or medical condition that is likely to impede in the successful completion of the study
2. Participants with a history of post-concussion headache or new daily persistent headache
3. Participants with a diagnosis of medication overuse headache
4. Participants with cardiac, renal or hepatic disease (assessed by the site investigator)
5. Participants with complex regional pain syndrome-II
6. Participants with abnormal ECG findings at baseline (as determined by the investigator)
7. Participants who are on the following medications: opioids, antipsychotics, antimanic, barbiturates, benzodiazepines, muscle relaxants, sedatives, or tramadol.
8. Participants with developmental delay or impairments including autism, cerebral palsy or intellectual disability.
9. Participants with a personal or family history of schizophrenia or psychotic disorders
10. Participants who are pregnant or breast/chest-feeding or plans to become pregnant within the study period or within three months of interventional product discontinuation
11. Participants who cannot commit to using contraception and refraining from recreational cannabis use and driving throughout the study period
12. Participants with known allergy to cannabinoids and/or palm/coconut oil

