**Cannabinoid and metabolite evaluation**

Monthly blood samples will be collected, and routine safety liver and renal lab test will be analysed locally at satellite sites. Dose-exposure-response will compare measurable cannabinoids and active metabolites (e.g., CBD, THC, ∆9-tetrahydrocannibivarin, cannabidivarin, cannabachromene) with changes in adverse events and other secondary endpoints. We will record steady-state minimum plasma concentrations (CSS,min) before each dose escalation and at the end of treatment. Samples will be collected via venipuncture by a registered phlebotomist or research nurse, before participants take the next dose of study intervention. Samples will be sent to [name] lab on dry ice and stored at -70°C, for stability and to avoid cannabinoid substrate binding. Samples for cannabinoid levels will be analyzed in the [name] lab by a validated LC-MS/MS protocol.[116]

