### Reporting of Pregnancy

Pregnancy tests (detection of human chorionic gonadotropin) will be completed using blood samples collected to investigate cannabinoid blood levels. At visit 1, a urine pregnancy test will be added on top of the blood pregnancy test to exclude patients with positive result from enrollment. Eligibility confirmation will still depend on the visit 1 blood pregnancy test result. Any participant who becomes pregnant will be offered to counsel and will be withdrawn from the study (investigational product use terminated).

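### The first dose is fixed as the day after visit 2 and does not wait for the visit 2 pregnancy result (minor safety point)

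*Protocol*

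**What the plan says.** Dosing and Administration sets the start of treatment by the calendar alone: a participant's "day 1 of IP dose starts the day after visit 2". Under Treatment Phase (visit 2 to visit 5), the product and dosing calendar are "shipped to their homes before visit 2", so on that text no later dispensing step could act as a hold.

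The Schedule of Activities lists a pregnancy test at all seven visits. Its note e gives both urine and blood tests at visit 1 and then blood alone: "Blood pregnancy test will be completed from visit 2- visit 7". Reporting of Pregnancy describes the sample: "Pregnancy tests (detection of human chorionic gonadotropin) will be completed using blood samples collected to investigate cannabinoid blood levels". The same section makes confirmation of eligibility depend on the visit 1 blood result. Inclusion criterion 4 likewise asks for a negative test at screening and does not ask for a repeat before the first dose.

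On a later pregnancy, Reporting of Pregnancy provides for counselling and withdrawal with the product stopped. Participant Discontinuation/Withdrawal from the Study lists pregnancy, and a newly developed exclusion criterion, among the reasons for withdrawal.

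**The concern.** The strictest pregnancy check stands at visit 1, when no drug will be taken for a month. At visit 2, the day before first exposure, the urine test is no longer done and no decision hangs on the blood result. A participant who conceives during the drug-free month would be picked up by a sample already in the schedule, but a site that follows the stated start day can let her begin while that result is pending. The rules that would stop her treatment act only once the pregnancy is known.

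The participants are aged 14 to 17, and the exclusion criteria bar "Participants who are pregnant or breast/chest-feeding or plans to become pregnant within the study period". What is at stake is a short, avoidable exposure to a CBD and THC product. There is also a small practical consequence: a participant found pregnant before any dose may be replaced under the withdrawal section, whereas one who has been dosed may not.

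**Working it through.** **Does any text hold the first dose?** The candidates, one by one:

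- Treatment Phase: blood is drawn monthly before the dose is increased. This times the draw, not receipt of a result, and it concerns increases rather than the first dose.
- Dose limiting toxicity and Discontinuation of Study Intervention: the listed reasons for not moving up a level do not name pregnancy or a pending test, and they do not govern the first dose.
- Exclusion Criteria, item 10: applied at enrolment.
- The two withdrawal provisions: these act once pregnancy is known.
- Reporting of Pregnancy: eligibility rests on the visit 1 blood result.

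None makes the start conditional on the visit 2 result.

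**Age of the last gating result at first dose.** From the Schedule of Activities, visit 1 is day 1 and visit 2 is day 30, each ±5 days. First dose = visit 2 + 1.

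- Nominal: 31 − 1 = 30 days.
- Shortest (visit 1 five days late, visit 2 five days early): (25 + 1) − (1 + 5) = 26 − 6 = 20 days.
- Longest (visit 1 five days early, visit 2 five days late): (35 + 1) − (1 − 5) = 36 + 4 = 40 days.

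**Exposure while the result is pending.** The Protocol gives no turnaround, so let the result arrive T days after visit 2, with T an assumption from 1 to 7. Full dosing days before the result day = max(0, T − 1). A dose taken on the result day itself is not counted.

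For the daily dose, Dosing and Administration says "the mid-point of the dose range will be selected to calculate the desired dose based upon the weight of the participants". At the first level this is (0.2 + 0.4) / 2 = 0.3 mg/kg/day CBD. The product holds 2 mg THC per 50 mg CBD, so THC is 0.3 × 2/50 = 0.012 mg/kg/day.

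| Assumed T (days) | Full dosing days before result | CBD (mg/kg) | THC (mg/kg) |
| --- | --- | --- | --- |
| 1 | 0 | 0 | 0 |
| 2 | 1 | 0.3 | 0.012 |
| 3 | 2 | 0.6 | 0.024 |
| 5 | 4 | 1.2 | 0.048 |
| 7 | 6 | 1.8 | 0.072 |

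The lower rows illustrate the scale only; no text in the Protocol supports one T over another.

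**Room for a delayed start.** Assume that the visit windows run from the nominal days. Visit 3 is then due by day 60 + 5 = 65. If visit 2 falls on day v and the start slips by s days, the first dose is on day v + 1 + s. The planned interval from first dose to visit 3 is 60 − 31 = 29 days. It is kept in full when 65 − (v + 1 + s) ≥ 29, that is, when v + s ≤ 35.

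- s = 5 is fully absorbed only if v ≤ 30.
- With v = 35 and s = 5, the first dose is on day 41 and at most 65 − 41 = 24 days remain, five fewer than planned.

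**The case against.** Several safeguards already apply. Visit 1 requires two kinds of pregnancy test. Those who cannot commit to contraception are excluded, and users of hormonal contraception are advised to add a barrier method. Blood testing is repeated at every visit, and a pregnancy leads to withdrawal. Monthly testing in any case accepts up to about a month of undetected exposure later on, at doses rising to 0.8-1.0 mg/kg/day, so a gate at the first dose removes little by comparison and would miss a very recent conception. Release of results may also be covered in site procedures or a manual that is not shown. All of this stands, and it is why the point is minor. It does not supply the missing condition: the start day is stated outright, and the test that could inform it is already scheduled the day before.

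Three stronger readings are tempting and are not supported.

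- A reader might infer that the pregnancy test goes to a distant laboratory, because it uses the cannabinoid blood and the Protocol says "Samples will be sent to [name] lab on dry ice", while only the "routine safety liver and renal lab test will be analysed locally at satellite sites". The text does not show where the pregnancy test is run. The Treatment Phase paragraph lists it next to the liver and renal tests, which points, without proof, towards local testing.
- A reader might infer that such a participant is enrolled in breach of exclusion 10. That criterion is applied at enrolment; a pregnancy arising afterwards falls under the withdrawal provisions.
- A reader might take a week of exposure as the expected harm. That rests wholly on an assumed turnaround.

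**Conclusion.** The point holds as a minor safety gap. The Protocol fixes an unconditional first dose the day after visit 2, and the last pregnancy result that gates treatment is nominally 30 days old by then (20 to 40 days with the windows). The visit 2 sample is drawn in time to help, but no text ties the first dose to its result.

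The gap opens only if a participant conceives in the drug-free month despite contraception and the result takes longer than a day. If the result is back by the next day, the exposure avoided is zero on the counting used here; otherwise it is a few days at 0.3 mg/kg CBD per day, the lowest level. Only those of the 20 participants who have reached menarche are concerned, and the Protocol gives no basis for estimating how many could be affected. Sites may hold the dose in practice, but the Protocol does not require them to. No endpoint, estimate or analysis depends on this.

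**What to change.** In Dosing and Administration, add that participants who have reached menarche take the first dose only after the site has confirmed a negative visit 2 blood pregnancy test, and that day 1 of the dosing calendar moves accordingly. Add a cross-reference in Reporting of Pregnancy.

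No visit or test is added, since the sample is already scheduled. The costs are these:

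- The start may slip by the laboratory turnaround. The visit 3 window absorbs a slip of up to 5 days in full only if visit 2 falls on or before day 30; otherwise the first dose level is shortened.
- The participant-specific dosing calendar is shipped with the product, so it may need correcting when day 1 moves.
- Local testing alongside the liver and renal tests would keep any delay short, but the Protocol does not establish that every site can do it.

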# INTRODUCTION

## Study Rationale

Randomized Control Trials (RCTs) and open-label studies have demonstrated the well-defined margin of safety and efficacy of CBD and CBD-enriched CHE in children with intractable epilepsy.[[1-9](#_heading=h.184mhaj)] Chronic headaches are one of the most common pain syndromes in adolescence, and despite numerous treatment options, roughly only half of adolescents with Chronic Headache (C) experience remission. CBD and other cannabis products are being used off-label for the treatment of chronic headaches. [[10](#_heading=h.3jtnz0s)] Prescription cannabinoids (nabiximols) and other cannabis-based products containing THC are currently being used off-label in adolescents with chronic headaches. The overall purpose of this open-label phase 2 study is to generate clinical evidence on the safety, and tolerability of a CBD-enriched CHE in adolescents suffering from chronic headaches. Furthermore, the ideal tolerated dose derived from this study will inform a future RCT to explore the efficacy of CBD-enriched CHE in a larger cohort. In this study, participants will receive escalating doses to a maximum of 1.0mg/kg of CBD/day to treat the chronic headaches. There have been many historical challenges with studying cannabis products and cannabinoids due to difficulties in consistently obtaining products, variable quality control and stigma associated with cannabis. Canada has the opportunity to be a world leader in cannabis research. The successful outcomes from this research project have the potential to create a meaningful impact on the lives of Canadian adolescents, given the high prevalence of chronic headaches, severe morbidity, and the current lack of effective treatment options.

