**Weaning Phase (from visit 6 to visit 7)**

After the baseline phase (one month) and the treatment phase (four months), participants will start the weaning schedule, which comprises incrementally reducing the dose leading to complete discontinuation of the study product. The intervention dose will be decreased in 0.2mg/kg increments every week. The intervention will be discontinued by visit 7. If the parents, adolescents, and healthcare providers feel an improvement in chronic headache, participants will be offered a medical cannabis authorization at the end of the study.

All participants and their caregivers will be invited to complete a post-study interview (telephone) about their experiences in the trial to inform future research. Questions will be asked around their overall impression of the trial, perceived risks, benefits, how it changed during the trial, outcome importance for future studies, challenges they encountered, and how we can improve our trial. More specific questions will also be asked on the usability and usefulness of the consent form, recruiting materials, outcomes measured and the daily headache collection tool.

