## Justification for Dose

Data on the pharmacokinetics related to the active constituent of Cannabis, i.e., CBD and THC, in adolescents are lacking. The CBD dose is extrapolated from safety data obtained in clinical trials in children with refractory epilepsy in the current study.[[1-7](#_heading=h.184mhaj), [118](#_heading=h.2i9l8ns)] Moreover, we made our present considerations about the dosing regimen based on the nature of our study product, namely an extract containing one of the major biologically active cannabinoids but also with pharmacologically relevant levels of other cannabinoids such as THC and cannabichromene.[[119](#_heading=h.xevivl)] CBD was found to be safe and well-tolerated in children with refractory epilepsy at a dose of 10-20mg kg/day. The suggested dose of CBD in the phase 2 study of refractory epilepsy was 10 mg/kg/day. [[1](#_heading=h.184mhaj), [4](#_heading=h.meukdy), [5](#_heading=h.36ei31r), [7](#_heading=h.45jfvxd), [113](#_heading=h.24ufcor), [118](#_heading=h.2i9l8ns)] The use of THC is associated with some risk of developing adverse effects on the central nervous system and peripheral organ system. However, these appear to be mitigated by the coadministration of CBD. THC possesses its significant pain-relieving potential at very low doses. [[120](#_heading=h.3hej1je)] The quantity of THC in our study product is 2mg per mL, with maximum THC doses only reaching 0.04mg/kg/day, which we do not expect to be associated with any adverse psychoactive reactions. In this study, the maximum dose of CBD will be less than 10 percent of the recommended dose of the CBD in the previous studies conducted in the pediatric population. We aim to keep the CBD dose as low as possible to reduce costs for families to confirm a tolerable dose and demonstrate efficacy in future clinical trials.

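### Mid-point dosing makes 0.9 mg/kg/day the highest assigned CBD dose, below the stated maximum of 1.0, and the last weaning step is 0.3 rather than the stated 0.2

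*Protocol*

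**What the plan says.** Table 4 in Dosing and Administration gives four monthly dose ranges: 0.2-0.4, 0.4-0.6, 0.6-0.8 and 0.8-1 mg/kg/day of CBD. The text of that section reduces each range to one value: "the mid-point of the dose range will be selected to calculate the desired dose". The weight used is the one taken at baseline. On rounding it says: "The final dose will be calculated by rounding off the nearest 1 mg of CBD". Its worked example is: "As an exemplary 24 kg, (0.3mg/kg/day) adolescent will receive a dose of 7 mg/day".

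On the maximum, the Study Rationale says that "participants will receive escalating doses to a maximum of 1.0mg/kg of CBD/day". Justification for Dose describes the product as having 2 mg of THC per mL, "with maximum THC doses only reaching 0.04mg/kg/day". It adds that the CBD maximum stays under 10 percent of the dose recommended in earlier paediatric work, and cites 10 mg/kg/day for the phase 2 epilepsy study. The Synopsis, the Schedule of Activities and Table 4 show only a range for the top level.

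The Treatment Phase section gives the first range and then says "Participant-specific dose will be prescribed by site investigator", without mentioning the mid-point.

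On weaning, the Weaning Phase section says "The intervention dose will be decreased in 0.2mg/kg increments every week", and Dosing and Administration gives the same rate. Table 5 lists weeks 1 to 4 as 0.6-0.8, 0.4-0.6, 0.2-0.4 and 0 mg/kg/day.

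**The concern.** The mid-point rule and the stated maximum do not describe the same top dose. A sponsor following the dosing rule assigns nobody 1.0 mg/kg/day, although the rationale tells the reader that escalation goes that far.

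This matters because the dose label carries the trial's result. Sample Size Determination describes a study meant to identify a safe dose, and the Study Rationale says the tolerated dose will inform a later randomised trial. The primary analysis describes adverse events across dosage levels, and the subgroup analyses also use dose level. If a report labels the top level with its range, or with the stated maximum, its reader may take forward a dose that was not assigned to anyone.

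The weaning text has a related fault: its stated weekly step does not match the last step in its own table.

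**Working it through.** **Inputs.** Dose ranges from Table 4; mid-point rule, rounding rule and worked example from Dosing and Administration; 50 mg CBD and 2 mg THC per mL from Study Intervention Description; stated maxima from Study Rationale (CBD 1.0) and Justification for Dose (THC 0.04); weaning ranges from Table 5.

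**Step 1: the plan's own figures.**
- Worked example: the mid-point of 0.2-0.4 is 0.3; 24 kg × 0.3 = 7.2, which rounds to 7 mg/day. This reproduces.
- THC maximum: 1.0 × 2/50 = 0.04 mg/kg/day. This reproduces, but from 1.0, the top of the range.

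**Step 2: assigned levels.** Mid-point = (low + high)/2; THC = CBD × 2/50.

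| Visit | Range (mg/kg/day) | Assigned CBD | Assigned THC |
| --- | --- | --- | --- |
| 2 | 0.2-0.4 | 0.3 | 0.012 |
| 3 | 0.4-0.6 | 0.5 | 0.020 |
| 4 | 0.6-0.8 | 0.7 | 0.028 |
| 5 | 0.8-1.0 | 0.9 | 0.036 |

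The levels are 0.2 apart, as the escalation text says. The highest is 0.9/1.0 = 90% of the stated maximum.

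**Step 3: size in mg/day at the top level.**

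| Baseline weight (assumed) | At 0.9 | At 1.0 |
| --- | --- | --- |
| 40 kg | 36 | 40 |
| 50 kg | 45 | 50 |
| 60 kg | 54 | 60 |
| 80 kg | 72 | 80 |

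**Step 4: can rounding close the gap?** Rounding adds at most 0.5 mg and the gap is 0.1 mg/kg × weight, so 1.0 could be reached only at 0.5/0.1 = 5 kg or less. Over assumed weights of 24 to 120 kg, the rounded top dose runs from 0.881 mg/kg/day (23 mg at 26.1 kg) to 0.920 (23 mg at 25 kg).

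**Step 5: the comparison with earlier studies.** Against 10 mg/kg/day, 0.9 is 9% and 1.0 is exactly 10%. The statement that the maximum is below 10 percent fits 0.9 and not 1.0. Within Justification for Dose, the THC figure therefore follows from 1.0, while the CBD comparison fits the mid-point.

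**Step 6: weaning.** Starting from 0.9, Table 5 at mid-points runs 0.7, 0.5, 0.3, 0. The steps are 0.2, 0.2, 0.2 and 0.3, so the last does not match the stated 0.2.

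**The case against.** The strongest reply is that a maximum is a ceiling. A dose of 0.9 lies inside 0.8-1.0 and below 1.0, and an upper bound that is not exceeded is conservative in a safety rationale. That reading is possible. However, the Study Rationale words 1.0 as something participants will receive, and nothing there tells the reader that the assigned top dose is lower.

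Several further points stand and limit the finding:

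- THC of 0.036 rounds to 0.04 at two decimals, so that figure alone proves no contradiction.
- The Synopsis gives only a range, so the explicit CBD maximum of 1.0 rests on the Study Rationale.
- The gap concerns the dose assigned on baseline weight. A participant who lost 10% of body weight would receive 0.9/0.9 = 1.0 mg/kg on current weight.
- The Protocol nowhere commits to a tolerability conclusion at 1.0, so the harm depends on how results are labelled.
- Table 5 lists every week, so the weaning schedule can be carried out; only its description is inconsistent.

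A reader might infer from the Treatment Phase sentence that investigators may choose any dose within a range, so that monthly steps vary and neighbouring levels overlap at shared endpoints. The text does not support this. The sentence most naturally says who writes the prescription, and a weight-based dose is participant-specific under any rule. Dosing and Administration sets the mid-point expressly to keep dosing consistent across centres.

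**Conclusion.** The point holds as an inconsistency between sections, not as a calculation error: each figure is correct for the dose it was computed from. Under the dosing rule the highest assigned level is 0.9 mg/kg/day CBD and 0.036 mg/kg/day THC, 10% below the maxima of 1.0 and 0.04. At 50 kg the difference is 5 mg of CBD and 5/25 = 0.2 mg of THC a day. The last weaning step is 0.3 against a stated 0.2.

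This assumes that sites follow the mid-point rule on baseline weight. The weights in the examples are assumptions, but the 10% does not depend on them before rounding. The gap is small and the four levels remain distinct. It still deserves correction, because it determines which dose the trial can say was tolerated. The documents do not settle which statement is intended, and no view is taken here on which dose or weaning step is right.

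**What to change.** - Reconcile the Study Rationale, Justification for Dose, and Dosing and Administration (with Table 4) so that the stated CBD and THC maxima follow from the dosing rule.
- Reconcile the weekly step in the Weaning Phase section and in Dosing and Administration with the last step in Table 5. In both cases the sponsor decides which statement applies.
- In the Treatment Phase section, add a cross-reference to the rule in Dosing and Administration.
- Label dose-level summaries by the assigned mg/kg/day, and limit the tolerability conclusion to the highest dose actually assigned. Any separate analysis plan should use the same labels.

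The cost is protocol wording and table labels, with no new data or procedures if the present dosing rule is kept. The downside is that the top dose the trial can quote becomes slightly lower if that rule stands.
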